### Study population

The study will be conducted at the Orthopedic Department of the UMCG. Patients between the ages of 18 and 75 who are admitted for primary cementless unilateral THA due to primary or secondary osteoarthrosis will be included. Patients with inflammatory polyarthritis or with a history of previous surgery on the affected hip will be excluded. Participation in the study is voluntary and patients have to provide informed consent before participation. The inclusion period is planned from March 2007 to May 2008.

### Intervention

#### Computer-navigated MIS

Patients in the MIS group will have surgery using the minimally invasive single-incision anterior approach [17]. The anterior approach is one of several possible approaches to the hip joint. Using special retractors, reamers and insertion handles it is possible to perform this procedure in a minimally invasive way, limiting the skin incision from about 15 cm. to about 8 cm. Advantage of the anterior approach is the possibility of using intermuscular spaces, avoiding muscle damage by cutting or detaching muscles and adding to the minimally invasive character of the approach.

An anterior incision centered over the hip joint is made in a supine patient. After division of skin and subcutis, the intermuscular space between the m. tensor fascia latae and the m. sartorius is identified and the overlying fascia is opened. The intermuscular plane between the m. tensor fascia latae and the m. sartorius is developed further down to the hip capsule. Subsequently the hip capsule is opened, allowing access to the hip joint. Preparation of the hip for implantation of a hip prosthesis can take place now, by in situ performance of osteotomy of the femoral neck, removal of the femoral head and reaming of the acetabulum, followed by insertion of an uncemented acetabular cup. After reaming of the femur an uncemented femoral component can be placed, followed by placement of a head on the femoral component, repositioning of the joint and closure in layers.

To optimize placement of the acetabular and femoral components of the total hip prosthesis, a computer navigation system (Stryker^® ^Navigation System iNstride Hip, Stryker Corporation, Kalamazoo, MI, U.S.A.) will be used. In order to use computer navigation it is necessary to place two trackers on the patient, which are used by the computer for referencing. These trackers are temporarily fixed on the patient by a small anchoring pin in the iliac crest and on the lateral side of the distal femur. These pins will cause no additional morbidity.

#### Conventional technique

Patients in the conventional technique group will have surgery using a standard posterolateral approach, in which the patient is placed in a lateral position. After transsection of the subcutis, the fascia latae and glutae are split. Next, the short external rotators are cut at the level of their insertion at the greater trochanter, so this approach is not muscle-sparing. After retraction of the short external rotators backwards, the hip capsule becomes visible and can be incised, allowing access to the hip joint. The rest of the operation will essentially take place in the same manner as the minimally invasive surgical technique.

In the computer-navigated MIS group as well as in the conventional technique group, the same femoral component (ABG II, Stryker Corporation) and acetabular cup (Trident^® ^Cup with X3 or Ceramic inlay, Stryker Corporation) will be used. The anesthetic, analgesic and postoperative physical therapy protocols will be standardized in both groups.

### Measurements

In this study, recovery is operationalized as the proportion of subjects with normal gait (no limping during walking) and as the self-reported functional status and health-related quality of life. Measurements will take place preoperatively (day of admission) and perioperatively, and 6 weeks and 3 and 6 months postoperatively. The amount of limping and self-reported functional status and health-related quality of life will be assessed preoperatively as well as postoperatively. Perioperative complications will be registered. Evaluation of prosthesis positioning will take place 6 weeks and 6 months postoperatively. The economic evaluation will focus on differences in costs between computer-navigated MIS and conventional THA technique. The evaluation will be performed from a societal perspective; costs within and outside the healthcare sector will be registered over a period of 6 months. Demographic data, diagnosis, height, weight and BMI, and ASA and Charnley classifications will also be recorded preoperatively.

#### Gait analysis

Functional status will be recorded objectively by means of gait analysis using body-fixed sensors. A major advantage of the body-fixed sensor-based approach is that these methods can be applied under real-life conditions; no expert laboratory is needed, and measurements can be made over longer periods of time and gait distances [18].

As walking is by far the most important aspect of functional status, the focus will lie on it – especially the extent of limping during walking (Duchenne limp), given that this is an evident indication of return to a normal gait. Gait parameters, such as accelerations and angular velocities of the upper trunk and pelvis, walking speed and step length, will be assessed while walking at slow, preferred and fast speeds, and while performing an additional attention-demanding task.

Limping can be measured by new methods and new hardware, both of which have been used in ongoing UMCG projects where gait function together with other measures are studied in patients after a hip or knee arthroplasty. Recent pilot work [19] has resulted in a new approach to assess compensatory movements of the trunk during walking. After the accuracy of this new method was confirmed by laboratory experiments, a field experiment showed that measures of pelvic and thoracic movements were related to (mean) walking speed, step length and step duration. The mean peak amplitudes in patients with and without Duchenne limp showed small but systematic differences [19]. It can be concluded that the new method is valuable for the assessment of compensatory trunk movements during gait. The approach allows for the simultaneous assessment of gait parameters and movements of the upper and lower trunk based on a combination of movement sensors.

#### Self-reported functional status and health-related quality of life

Self-reported functional status and health-related quality of life will be measured with questionnaires. The WOMAC will be used as a disease-specific outcome instrument to measure functional status. The SF-36 and EuroQol 5D are generic questionnaires and will be used to measure health-related quality of life. Patients' satisfaction with the results of the surgical procedure will be measured with the Patient Satisfaction Scale.

The Western Ontario and McMaster Universities Osteoarthritis Index (WOMAC) consists of three subscales measuring pain, stiffness and physical functioning. Patients have to score on a five-point Likert scale. The WOMAC has shown high validity and reliability [20]. The Dutch version of the WOMAC has also been considered valid and reliable [21]. The MOS 36-item Short Form Health Survey (SF-36) gives an indication of health-related quality of life, and is considered to be valid, reliable and reproducible [22]. The SF-36 is composed of 36 questions, organized into 8 multi-items scales: physical functioning, role limitations due to physical health problems, bodily pain, general health perceptions, vitality, social functioning, role limitations due to emotional problems and general mental health [22]. The WOMAC and SF-36 are the most widely used questionnaires in THA research [23,24]. The EuroQol 5D is a widely used and validated generic instrument that consists of 5 dimensions: mobility, self-care, usual activities, pain/discomfort and anxiety/depression [25]. The EuroQol 5D has to be seen as additional to the SF-36 and is embedded in this study protocol, as it is especially useful in combination with the economic evaluation that will be performed. The Patient Satisfaction Scale comprises 4 questions about satisfaction with pain relief, with improvement in function for home/yard work and with improvement in function for recreational activity, as well as overall satisfaction with surgery [26].

#### Perioperative measurements

Perioperatively, average surgical time, intraoperative blood loss, in-hospital transfusion rate and length of skin incision will be recorded.

#### Radiographic evaluation

At the Orthopedic Department of the UMCG a new digital measurement method has been developed with which postoperative measurements can be executed to objectify and quantify parameters of the quality of positioning of a total hip prosthesis [27]. The new procedure employs digital measurement techniques, which are far more reliable than conventional analogue techniques [28-30]. A radiographic evaluation of several parameters will take place by means of this new digital measurement method. Leg length differences, varus and valgus positioning of the stem, and inclination and anteversion of the acetabular component will be determined.

#### Economic evaluation

Outcomes of the above-mentioned measurements will be related to costs in additional economic analyses. These analyses will provide information on the probable cost effectiveness of computer-navigated MIS compared to conventional THA technique in the Dutch healthcare system.

Direct medical costs to be assessed include costs of computer-navigated MIS and conventional THA technique, blood transfusions, hospital admissions and costs related to length of hospital stay. In order to facilitate comparisons with other economic evaluations, unit prices (the price of one unit of each cost type included) will be based mainly on Dutch standard prices [31]. A questionnaire on medical costs outside the hospital (including physiotherapy, visits to general practitioners, nursing care and medication) and other (nonmedical) costs (e.g. absence of work) will be administered to the patients.

### Sample size

It is our hypothesis that computer-navigated MIS will lead to better recovery during the early postoperative period (3 months), and at least as good at 6 months postoperatively. In order to detect a difference of 0.254 in the proportion of subjects with normal gait after 3 months of follow-up with 80% power at a significance level of 0.05 in a one-sided test of a difference between two proportions, two groups of 50 subjects are required. With an expected dropout rate of 10%, a total of 110 patients is needed. At 6 months, the effect of MIS and conventional THA technique on gait (limping) will be compared in a non-inferiority setting. To establish non-inferiority, the lower bound of the 95% confidence interval of the difference between the two treatment groups will be compared with a non-inferiority margin delta. If the whole confidence interval of the difference between the two treatments is smaller than the non-inferiority margin delta, non-inferiority is established. The non-inferiority margin delta is chosen in this study at a value of 0.10, indicating that a difference in proportion of subjects with a normal gait of 0.10 is considered clinically equivalent. To deduce non-inferiority with 80% power at a significance level of 0.05 with expected proportions of subjects with normal gait of 0.95, using a non-inferiority margin delta of 0.10, two groups of 60 subjects are required. With an expected dropout rate of 10%, a total of 132 patients is needed.

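### The 6-month non-inferiority rule names the lower confidence bound in one sentence and sets an upper-bound condition in the next, and no sign convention makes both correct

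*Protocol article*

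**What the plan says.** All of this stands in the Sample size section of the protocol article.

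- Setting: "At 6 months, the effect of MIS and conventional THA technique on gait (limping) will be compared in a non-inferiority setting".
- First statement of the rule: "the lower bound of the 95% confidence interval of the difference between the two treatment groups will be compared with a non-inferiority margin delta". It gives neither the direction of the comparison nor the order of subtraction.
- Second statement, directly after it: "If the whole confidence interval of the difference between the two treatments is smaller than the non-inferiority margin delta, non-inferiority is established".
- Margin: "The non-inferiority margin delta is chosen in this study at a value of 0.10", without a sign. The scale is the proportion with normal gait, where higher is better: "a difference in proportion of subjects with a normal gait of 0.10 is considered clinically equivalent".
- Planning figures: "To deduce non-inferiority with 80% power at a significance level of 0.05", "with expected proportions of subjects with normal gait of 0.95", and "two groups of 60 subjects are required". The sidedness of this 0.05 is not stated.

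The Statistical analysis section does not mention non-inferiority, and no other section restates the rule.

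**The concern.** A non-inferiority rule needs an order of subtraction, a signed margin and the confidence limit that decides. Here the first two are missing, and the two sentences disagree on the third. The first makes the lower limit decisive. The second makes the upper limit decisive.

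This is the success criterion for one of the trial's two recovery hypotheses, that MIS is at least as good at 6 months. It also drives the larger of the two sample sizes (132 against 110). A rule that can be read in opposite directions leaves the choice of reading open until the data are seen. At least one literal reading accepts a technique that is clearly worse and refuses one that is clearly better.

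**Working it through.** **Inputs, all from the Sample size section:** margin 0.10; expected proportion 0.95 in both groups; 60 per group; 95% confidence interval; power 80%; significance level 0.05.

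**Step 1: the plan's own figure.** For equal true proportions p, n per group = (z for alpha + z for power)² × 2p(1−p) / margin².

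- One-sided 0.05: (1.645 + 0.842)² × 2 × 0.95 × 0.05 / 0.10² = 58.7, so 59. The stated 60 is reproduced.
- One-sided 0.025, the level of a limit from a two-sided 95% interval: (1.960 + 0.842)² × 0.095 / 0.01 = 74.6, so 75. The stated 60 is not reproduced.

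**Step 2: the two sentences under each sign convention.**

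| Difference | Sound rule | Lower-bound sentence | Whole-interval sentence |
|---|---|---|---|
| MIS − conventional | lower limit > −0.10 | right limit, but the margin needs a minus sign | wrong: satisfied when MIS is poor |
| Conventional − MIS | upper limit < +0.10 | wrong limit | right |

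Neither row makes both sentences correct. Recasting the outcome as the proportion limping only swaps the rows. Reading the margin as −0.10 does not rescue the second sentence: under MIS minus conventional it would then pass only when MIS is shown to be more than 10 points worse.

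**Step 3: one concrete result.** MIS 45/60 = 0.75, conventional 57/60 = 0.95. MIS minus conventional = −0.20. Standard error = √(0.75 × 0.25/60 + 0.95 × 0.05/60) = 0.0626. The 95% interval is −0.20 ± 1.96 × 0.0626, that is −0.323 to −0.077. The whole interval lies below 0.10, so the second sentence taken literally establishes non-inferiority, although MIS is significantly worse.

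**Step 4: how often.** All 61 × 61 outcomes were enumerated with exact binomial probabilities, 60 per group and two-sided 95% Wald limits. The difference is MIS minus conventional.

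| True MIS / conventional | Whole interval < 0.10 (as written) | Lower limit > −0.10 (sound) |
|---|---|---|
| 0.80 / 0.95 | 0.993 | 0.004 |
| 0.85 / 0.95 (at the margin) | 0.969 | 0.037 |
| 0.95 / 0.95 | 0.72 | 0.72 |
| 0.95 / 0.80 | 0.004 | 0.993 |

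The two rules agree only when the techniques are equal, which is the planning case, so the sample size calculation cannot reveal the fault.

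**Step 5: conventional minus MIS.** The whole-interval sentence is then the sound rule (0.004 at 0.80 / 0.95). If one supplies the missing direction as lower bound below 0.10, a 15-point deficit passes with probability 0.88 and a 20-point deficit (0.75 / 0.95) with 0.65. These two figures depend on that supplied direction.

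**Step 6: reading 'smaller than' as absolute size.** The whole interval must then lie between −0.10 and +0.10, which is an equivalence test. It passes 0.002 of trials at 0.80 / 0.95, but also only 0.002 at 0.95 / 0.80, and its power at 0.95 / 0.95 is 0.44.

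**Step 7: power of the sound rule at 60 per group, 0.95 in both.** Exact power is 0.72 with the lower limit of a two-sided 95% interval and 0.83 with a one-sided 95% limit. The normal formula gives 0.71 and 0.81.

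**The case against.** A reader might infer that, whichever way the difference is taken, one of the two sentences declares non-inferiority for a clearly worse MIS. The document does not support that. Its first sentence says only that the lower bound is compared with the margin; it states no pass condition. Only the second sentence says when non-inferiority is reached, and for conventional minus MIS that sentence is correct. The defect is then a single word, lower for upper, and the 0.88 and 0.65 of Step 5 belong to a rule that the reader has completed.

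It can also be said that the intent is plain. The hypothesis is at least as good, the margin is on the proportion with normal gait, and equal proportions are assumed. A sensible analyst would not claim non-inferiority from an interval of −0.323 to −0.077. The 0.99 describes the literal rule under one sign convention; it is not a forecast of what the analysts will do. The absolute-size reading has some footing too, since the article calls a difference of 0.10 clinically equivalent, and it would not pass a worse MIS.

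These points limit the size of the claim but do not remove the contradiction. The 0.99 arises under the very convention that the lower-bound sentence suits. The absolute-size reading does not match that sentence either, would refuse a better MIS, and falls far short of the stated 80% power. Nor is this a detail left to a fuller document: the article states the criterion, and states it inconsistently.

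**Conclusion.** The point holds: the 6-month decision rule is internally inconsistent, and no sign convention makes both sentences correct. Its consequence depends on the reading.

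- MIS minus conventional, second sentence literal: non-inferiority with probability 0.99 for a 15-point deficit and 0.004 for a 15-point advantage.
- Conventional minus MIS: the second sentence is sound, and the first should name the upper bound.
- Absolute size: an equivalence test with 0.44 power in the planning case.

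The probabilities assume 60 analysed per group, independent patients and Wald limits from a two-sided 95% interval. The fault in the wording does not itself invalidate the 60 per group, which reproduces at one-sided 0.05. Any repair must still settle the level of the interval, because a two-sided 95% limit and 80% power do not go together at that size. The correction is needed before analysis, since it fixes the criterion for a main hypothesis.

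**What to change.** Replace both sentences with one:

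> Difference = proportion with normal gait, computer-navigated MIS minus conventional; non-inferiority is concluded if the lower 95% confidence limit lies above −0.10.

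Then state which limit is meant:

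- a one-sided 95% limit, which matches the 60 per group (exact power about 0.83); or
- the lower limit of a two-sided 95% interval, with power at 60 per group restated as about 72% instead of 80%. By the formula in Step 1, 80% power would need 75 per group.

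The rewording costs one sentence, changes neither the margin nor the data, and needs no extra patients under the first option. Under the second, the cost is either a lower stated power or a larger trial.

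### The 6-month non-inferiority sample size of 60 per arm fits a one-sided 5% test, but the decision rule, read naturally, is one-sided 2.5%, which gives about 71% power instead of 80%

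*Protocol article*

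**What the plan says.** All the relevant text is in the Sample size section of the protocol article, which describes the 6-month gait comparison in two steps.

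- **Decision rule.** The section says that "the lower bound of the 95% confidence interval of the difference between the two treatment groups will be compared with a non-inferiority margin delta". It then adds: "If the whole confidence interval of the difference between the two treatments is smaller than the non-inferiority margin delta, non-inferiority is established". The margin is fixed: "The non-inferiority margin delta is chosen in this study at a value of 0.10".
- **Sample size.** The planning assumptions are given as follows: "To deduce non-inferiority with 80% power at a significance level of 0.05 with expected proportions of subjects with normal gait of 0.95". The result is that "two groups of 60 subjects are required", raised to 132 in total for 10% dropout.

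The non-inferiority sentence does not give the sidedness of the 0.05. The same section does call the 3-month superiority test one-sided at 0.05. The Statistical analysis section sets a general threshold of 0.05, again without sidedness. Nowhere is the 95% interval described as one-sided, and no 90% interval is mentioned.

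**The concern.** A two-sided 95% interval leaves 2.5% in each tail, so judging non-inferiority on its lower limit is a one-sided 2.5% test. If the sample size was worked out at one-sided 5%, planning and decision use error rates that differ by a factor of two, and the stated power does not belong to the stated rule.

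Two things are at stake. First, this calculation sets the size of the trial: the 3-month comparison needs only 110 patients, and the total of 132 comes from the 6-month one. An outcome at least as good at 6 months is also one of the two parts of the recovery hypothesis. Second, the interval level can decide the conclusion. A result whose 90% lower limit clears the margin but whose 95% lower limit does not would pass under one reading and fail under the other.

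**Working it through.** **Inputs, all from the Sample size section:** proportion with normal gait 0.95 in both arms (true difference zero), margin 0.10, power 80%, significance level 0.05 with sidedness not given, 60 per arm, 10% dropout.

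**Formula (normal approximation, unpooled variance):**

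n per arm = (z_α + z_β)² × 2 × 0.95 × 0.05 / 0.10² = (z_α + z_β)² × 9.5, with z_β = 0.8416.

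**Reproducing the stated 60**

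| One-sided α | Two-sided interval with the same lower limit | Calculation | n per arm |
|---|---|---|---|
| 0.05 | 90% | (1.6449 + 0.8416)² × 9.5 = 58.7 | 59 |
| 0.025 | 95% | (1.9600 + 0.8416)² × 9.5 = 74.6 | 75 |

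The first row matches 60 within rounding; the second does not. Other standard variants also miss it. A restricted-variance (Farrington-Manning) calculation gives 78 at one-sided 0.05 and 100 at 0.025. Two one-sided tests for equivalence give 82 and 100. The total follows as 2 × 60 × 1.10 = 132.

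**Power at 60 per arm**

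- Standard error: √(2 × 0.95 × 0.05 / 60) = 0.0398.
- Margin in standard errors: 0.10 / 0.0398 = 2.513.
- Lower limit of a two-sided 95% interval: Φ(2.513 − 1.960) = Φ(0.553) = 71.0%. Exact binomial enumeration with a Wald interval gives 71.7%.
- Lower limit of a two-sided 90% interval, which is the same as a one-sided 95% bound: Φ(2.513 − 1.645) = Φ(0.868) = 80.7%. Exact enumeration with a Wald interval gives 82.7%.

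**Size needed for 80% under the 95% rule.** 75 per arm is 15 more than stated (15/60 = 25%). With the protocol's own dropout inflation that is 2 × 75 × 1.10 = 165 patients. Dividing by 0.90 instead gives 84 per arm, or 168.

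**Where the two readings part.** At the planning standard error, the 95% half-width is 1.960 × 0.0398 = 0.078 and the 90% half-width is 1.645 × 0.0398 = 0.065. An observed deficit for the navigated arm between 0.10 − 0.078 = 0.022 and 0.10 − 0.065 = 0.035 would therefore meet the margin on the 90% interval and miss it on the 95% interval.

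**The case against.** The best defence is that a one-sided 95% lower bound was meant all along. The first sentence of the rule compares only the lower bound with the margin, and the 3-month test in the same section is explicitly one-sided at 0.05. On that reading planning and decision agree and power is about 81%. This cannot be excluded. Against it, the next sentence speaks of the whole interval, which suggests an ordinary two-sided one, and the label given to the 3-month test is not repeated for this one. An analyst following the text would compute a standard 95% interval.

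It is also fair to say that the mismatch is conservative. The 95% interval is the stricter rule, so false claims of non-inferiority are not inflated; the cost is about 9 points of power (80 − 71). The 3-month calculation is untouched.

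Three stronger readings are tempting, and the document supports none of them.

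- **That the protocol states a one-sided 5% basis for the 60.** It does not. That basis is inferred, as the only standard variant tried that fits, and it yields 59, not exactly 60.
- **That the trial will actually deliver 71%.** The figure is conditional on 0.95 in both arms, a Wald-type interval and individual randomization. The article describes cluster randomization, and the calculation has no design effect. Any positive intracluster correlation would lower power under either reading, but that is a separate matter.
- **That the true figure is much lower still.** A Newcombe score interval at 60 per arm gives about 58% at the 95% level, but also only about 73% at the 90% level; the article names no interval method. With 0.90 in both arms, the normal approximation gives 45% (95% interval) and 57% (90% interval). Both the Newcombe interval and the 0.90 are assumptions brought from outside the document. They lower power under both readings and are not part of the inconsistency.

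**Conclusion.** The inconsistency stands on the natural reading of the text. The sidedness of the planning 0.05 is not given, the stated 60 per arm fits only one-sided 0.05, and a two-sided 95% interval makes the decision one-sided 2.5%. Power for the 6-month claim is then about 71%, so the chance of missing true non-inferiority is about 29% where the plan implies 20%. Reaching 80% would take 75 per arm. If a one-sided 95% bound was intended, the plan is coherent at about 81% and the defect is one of wording. Because the choice could decide the 6-month conclusion, the text should settle it either way.

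**What to change.** Keep 132 patients and make the two statements agree before the 6-month data are analysed. There are two ways to do this:

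1. Keep the two-sided 95% interval, state that this is a one-sided 2.5% test, and restate power at 60 per arm as about 71%.
2. State that non-inferiority is tested one-sided at 5% on the lower limit of the two-sided 90% interval, and keep power at about 80% (normal approximation).

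In either case, give the sidedness explicitly in the non-inferiority sentence. If power under another interval method or another expected proportion is added, label it as an assumption and report it for the level chosen.

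The cost is one restated power figure or one restated confidence level, with no extra patients. Holding both the two-sided 95% interval and 80% power would instead require 75 evaluable patients per arm, about 165 to 168 in total.

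### Sixty per group does not give 80% power for 6-month non-inferiority once the limit roughly keeps its error rate: about 73% at one-sided 5%, about 58% under the stated 95% interval read as two-sided

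*Protocol article*

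**What the plan says.** The point lies in the Sample size section of the protocol article, in the part on 6 months.

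- **Planning rates:** the calculation is made "with expected proportions of subjects with normal gait of 0.95", so the true difference is taken as zero.
- **Margin:** "The non-inferiority margin delta is chosen in this study at a value of 0.10", on the absolute scale.
- **Error and power:** "To deduce non-inferiority with 80% power at a significance level of 0.05". This sentence does not say whether 0.05 is one- or two-sided.
- **Decision rule:** "the lower bound of the 95% confidence interval of the difference between the two treatment groups will be compared with a non-inferiority margin delta".
- **Result:** "using a non-inferiority margin delta of 0.10, two groups of 60 subjects are required", and then "With an expected dropout rate of 10%, a total of 132 patients is needed".

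Neither the Sample size nor the Statistical analysis section names the sample-size formula or the type of interval.

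**The concern.** At a proportion of 0.95 the simple normal approximation for a difference in proportions is on weak ground, because 60 x 0.05 = 3 patients per arm are expected to limp. The Wald standard error is then often too small and the lower bound too close to the observed difference. This flatters power and lets through too many techniques that are worse by the full margin.

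The calculation and the decision rule may also use different error levels. A size that fits one-sided 0.05 sits beside a rule based on a 95% interval, whose lower bound is a one-sided 0.025 bound if the interval is two-sided.

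At stake is the claim that the navigated minimally invasive technique is at least as good at 6 months. This is one of the two recovery hypotheses, and it sets the larger of the two enrolment totals (132 against 110). If the true chance of missing non-inferiority is well above 20%, a failed non-inferiority result will be harder to interpret than the article suggests.

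**Working it through.** **Inputs** (all from Sample size): 0.95 in both groups; margin 0.10; power 80%; significance level 0.05; 60 per group; 10% dropout.

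**1. Reproducing the 60.** The unpooled normal approximation is n = (z_alpha + z_power)² x [p1(1 - p1) + p2(1 - p2)] / margin².

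- Variance term: 2 x 0.95 x 0.05 = 0.095.
- One-sided 0.05: (1.645 + 0.842)² x 0.095 / 0.01 = 58.7, so 59 per group. This matches 60 within rounding.
- One-sided 0.025: (1.960 + 0.842)² x 0.095 / 0.01 = 74.6, so 75. No match.
- Farrington-Manning (score) formula: 78 at one-sided 0.05 and 100 at one-sided 0.025. No match.

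Formula power at 60 per group: 0.10 / √(0.095/60) = 2.513. Then Φ(2.513 - 1.645) = 80.7% at one-sided 0.05, and Φ(2.513 - 1.960) = 71.0% at one-sided 0.025.

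**2. Exact behaviour at 60 per group.** For each rule of the form *lower limit above -0.10*, binomial probabilities are summed over all 61 x 61 possible outcomes. Power is taken at 0.95 v 0.95. Error is taken where the new technique is worse by exactly the margin, mainly 0.85 v 0.95.

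| Limit | Bound | Power | Error, 0.85 v 0.95 | Error, 0.89 v 0.99 |
|---|---|---|---|---|
| Wald | one-sided 5% | 82.7% | 6.7% | 10.5% |
| Newcombe | one-sided 5% | 72.6% | 5.0% | 4.2% |
| Farrington-Manning | one-sided 5% | 72.6% | 4.7% | 4.2% |
| Wald | two-sided 95% interval | 71.7% | 3.7% | 6.0% |
| Newcombe, Farrington-Manning | two-sided 95% interval | 58.1% | 2.1% | 2.0% |

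Miettinen-Nurminen gives the same power as the other two score-type limits at this size (72.6% and 58.1%).

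**3. Separating the two causes.**

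- *Approximation alone*, at the one-sided 0.05 that yields about 60: exact power is 82.7% with Wald and 72.6% with a score-type limit. Against the stated 80%, the shortfall is about 7 points.
- *Sidedness alone*, keeping Wald: 82.7% falls to 71.7%.
- *Both together*: 58.1%, about 22 points below the stated 80%.

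**4. Robustness.**

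- Binomial power moves in steps, but 60 is not an unlucky size. Newcombe power for 58 to 62 per group is 72-74% at one-sided 5% and 56-61% with the 95% interval.
- After dropout, 132 x 0.90 = 118.8, or about 59 per group, so the analysed number is no larger than 60.
- Other limits at 60 per group, one-sided 5% and 95% interval respectively: Agresti-Caffo 76.0% and 67.4% (error 5.1% and 3.0% at 0.85 v 0.95); exact unconditional 67.4% and 54.8%. No limit tried with error close to its nominal level reaches 80%.
- For exact power of at least 80%, the score limit needs about 72 per group at one-sided 0.05 or about 95 at one-sided 0.025.

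**The case against.** The strongest reply is that the choice of interval belongs in an analysis plan, that this is a condensed article, and that planning from a simple formula is common practice. No Wald analysis is specified, and the Statistical analysis section speaks of random effect models, so an independent-binomial calculation may not describe the final analysis. It stands that leaving the interval unnamed is no fault in itself. But the article does state a result, 80% power from 60 per group. An unseen plan that named a score interval would correct the error rate, yet it would contradict the published 80% rather than support it.

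A reader might infer four stronger things that the documents do not support:

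- *That the normal approximation alone brings power down to 58%.* It does not. Like for like the figure is about 73%. The lower figure also contains the mismatch between a one-sided 0.05 calculation and a 95% interval rule, which is a separate defect.
- *That the written decision rule inflates error at the planning rates.* The article states 0.05 and nowhere 2.5%. A Wald bound from a two-sided 95% interval has an error of 3.7% at 0.85 v 0.95. That is above 2.5% but below the stated 0.05, and it passes 5% only at control rates of about 0.98 and higher (5.2% at 0.98, 6.0% at 0.99). The 6.7% and 10.5% belong to a one-sided 5% Wald bound.
- *That the 60 is known to be a Wald figure.* No formula is named and the arithmetic gives 59. The origin is inferred from the formulas tried.
- *That score limits hold their level exactly.* They do so approximately. At one-sided 5%, Newcombe reaches 5.4% at 0.80 v 0.90, and both Newcombe and Farrington-Manning reach 5.3% at 0.90 v 1.00. These excesses are far smaller than Wald's.

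**Conclusion.** The point holds in this limited form. The stated 80% is reached only by pairing a one-sided 5% bound with the Wald limit, whose error at the planning rates is 6.7% rather than 5%. With a score-type limit at one-sided 5%, 60 per group gives about 73%. If the 95% interval in the decision rule is two-sided, power is about 72% even with Wald and about 58% with a score-type interval. The chance of missing true non-inferiority is then about 27% or 42%, against the 20% implied.

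These figures assume independent patients, 60 analysed per arm, a true rate of 0.95 in both groups, and a two-group comparison of proportions. They ignore cluster randomisation, for which any allowance would normally lower power further. The range 58% to 73% applies to score-type limits; other limits with roughly nominal error shift it by about 3 to 9 points. The matter should be corrected, but it does not invalidate the design.

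**What to change.** In the Sample size section, or in the analysis plan with a matching correction to the stated power:

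1. Specify a score-type interval (Newcombe, Miettinen-Nurminen or Farrington-Manning) for the 6-month risk difference in normal gait.
2. State whether the lower bound is a one-sided 5% bound or comes from a two-sided 95% interval, and use the same level in the calculation and the decision rule.
3. Restate the power of 60 per group as about 73% (one-sided 5%) or about 58% (two-sided 95% interval), before any allowance for cluster randomisation.

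This takes two or three sentences and does not itself change enrolment. The downside is a less favourable stated power. If the sponsor wants to keep 80%, the sizes to weigh are about 72 or 95 analysed per group, again before clustering and dropout.
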